#### Secondary outcomes

Information about psycho-oncology services, treatment satisfaction, patient competence and quality of life are secondary outcomes as well as acceptance and practicability of the OptiScreen-Training, assessment of access to and utilization of support services, barriers and facilitating factors for the utilization of psycho-oncological services.

#### OptiScreen questionnaire

An individual questionnaire (OptiScreen questionnaire) was developed to assess patients' experiences with screening and psycho-oncology. Questions address psychological support prior to disease, as well as experiences with psycho-oncologists during current hospitalization or need for further psychological support after discharge (use of support and need). Attitudes toward psycho-oncology, barriers, and satisfaction with support services were also recorded (satisfaction and barriers). In addition, experiences with caregivers regarding information about psycho-oncology, brochures received, and the screening questionnaire are asked (information and screening).

#### Assessment sheet psycho-oncological consultation

For psycho-oncologists, a questionnaire and documentation sheet ("assessment sheet psycho-oncological consultation") is prepared, which is to be completed by the psycho-oncologist after the psycho-oncological consultation in the hospital. The assessment sheet contains information about the patient and duration of the psycho-oncological consultation, information about the cancer diagnosis and treatment, level of information of the patient about psycho-oncology (information provided by the medical treatment team, receipt of a flyer about psycho-oncology, knowledge about the upcoming psycho-oncological consultation), patient's need for psycho-oncological care, patient's competence to recognize own need for psycho-oncological support, patient's openness to psycho-oncological support, patient's psychological distress/illness as well as previous psychological illnesses, type, extent and quality of psycho-oncological exchange with current oncological treatment team, environmental factors (organization, materials, facilities, patient's accessibility, documentation, etc.) to ensure psycho-oncological support, degree of burden of the psycho-oncologist by the psycho-oncological consult. In addition, the patients' symptom and stress areas will be evaluated as a third-party assessment in comparison to the patient survey. Synchronous to the patient survey, short versions or adapted parts of the questionnaires will be used as external evaluation (Table 1).

#### Training evaluation questionnaire for nurses

The training evaluation questionnaire includes sociodemographic data, questions about current knowledge and experience with psycho-oncology and the screening measures. Pre-training expectations and attitudes toward screening are asked. Questions are answered on a five-point Likert scale (1 = not at all to 5 = very much).

Additionally the post-evaluation contained the German Training Evaluation Inventary (Ritzmann et al. 2014) which shows good internal consistency (Cronbachs *α* = 0.73). It includes five scales on training outcomes dimension (perceived fun, perceived difficulty, perceived usefulness, knowledge acquisition, attitude) and five scales on training design dimension (problem-based learning, activation of prior knowledge, demonstration, application, integration). The respective items can be answered on a five-point Likert scale (0 = I disagree to 4 = I strongly agree). High sum scores represent a higher rating of the respective underlying dimension.

#### Statistical measures

First, the primary and secondary outcomes as well as all patient characteristics are analyzed descriptively together and separately for the two groups (means, standard deviations, frequencies). The primary outcome, psychological distress, is analyzed by ANCOVA (analysis of covariance) including variables such as tumor stage, age, and gender as covariates. This usually even increases the power of an ordinary *t* test. Missing values are replaced using multiple imputation. In sensitivity analyses, the results of the primary analysis are checked for consistency. Differences in secondary outcomes are evaluated between intervention and comparison groups or between appropriate subgroups analogous to the primary analysis using univariate or multivariate procedures or appropriate regression models. Depending on the distribution of the target parameter, binary or ordinal logistic mixed model regressions and linear mixed model regressions will be used. Before starting the analysis, the exact procedures are defined in a statistical analysis plan. Moderator as well as mediator analyses are used to identify barriers to take-up, as they can test complex relationships between several variables in the form of a priori models. The evaluation of the training will be analyzed using *t* tests (pre and post).

To control for possible selection effects that could lead to sampling bias, reasons for non-participation and sociodemographic and medical data of the non-participants will be analyzed. In this way, possible selection effects can be identified and the interpretation of results may be adjusted as necessary. Possible confounding variables are analyzed in inferential statistical analyses (e.g., regressions) using important covariates (age, gender, tumor entity, stage) as well as other theory-based influencing factors, e.g., physical comorbidities controlled.

Missing values due to drop-outs are replaced and can be predicted by means of multiple imputation, in that for the missing values, estimated values are used, which are calculated by distributing different predictors. This is done by taking all available relevant information of the data set into account and including random errors. The advantage is a low loss of information, since all variables remain included in the model. In addition, standard errors, which are moreover caused by the multiple repetition of the estimation process are randomly and realistically calculated and included.

Qualitative methods such as content analysis according to Mayring and Fenzl (2019) are used for the evaluations of the free responses.

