### Design

The study design is uncontrolled before and after pilot study. Measurement time points are a baseline measurement during the inpatient stay (t0) and a 3-month follow-up (t1 postal or online). As a comparison sample (CG, *N* = 300), screening data are collected 6 months prior to the introduction of the "OptiScreen-Training" on the same wards as after the introduction of the optimized screening, which thus corresponds to a care-as-usual (CAU) condition (Fig. 2). Care-as-usual refers to the identification of mentally distressed patients in the same way as is customary in their respective wards. Advantages of this approach are cost efficiency and practicality. After completion of the OptiScreen-Training, an additional *N* = 600 patients (intervention group, IG) will be surveyed at t0 and t1 (Fig. 2).

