### Procedure and recruitment

#### Patients

Cancer patients will be recruited via the respective visceral oncology centers of the three study sites. The eligibility criteria will be assessed by the study coordinators. If patients decline to participate in the study, a 3–5 min interview will be conducted to capture reasons for refusal, previous screening and psycho-oncology experiences, and information about the current disease. The participants receive the same questions in the questionnaire. If the inclusion criteria are fulfilled and the patient is interested in participating in the study, a detailed explanation is given in a personal interview (informed consent) after the initial contact with the patient. If the person declares their willingness to participate, a signed consent form is obtained.

In addition to the screening, the patients receive a questionnaire package (approximately 30–40 min) at t0 and t1 (Table 1). Furthermore, demographic, medical and treatment-related data are collected. The patients receive the questionnaires in person (at t0 during the inpatient stay) and by mail or e-mail as an online survey via link (at t1). The online questionnaire will be provided via a secure online survey platform (UniPark). Completed questionnaires will be collected by the study nurse and the study coordinators. If questionnaires are not received at t1, a reminder will be sent (by mail or e-mail) after 2 weeks.

**Table 1 Tab1:** Measurement instruments

Questionnaire	CG t0	CG t1	IG t0	IG t1
*Basic data*				
Demographic, medical and treatment-related data	x	x	x	x
*Screening*				
Distress (NCCN-DT)	x	x	x	x
Corona-DT	x	x	x	x
Knowledge about psycho-oncology (OptiScreen Questionnaire)	x	x	x	x
*Psychological functioning*				
Depression (PHQ-9)	x	x	x	x
Anxiety (GAD-7)	x	x	x	x
Quality of life (SF-8)	x	x	x	x
Fear of cancer recurrence (PA-F-KF)	x	x	x	x
Health literacy (HLS-EU-Q16)	x	x	x	x
Support needs (SCNS-SF34-G)	x	x	x	x
Social support (ISSS)/SSUK-8)	x	x	x	x
Body image (BIS)	x	x	x	x
Patient activation (PAM-13D)	x	x	x	x
Satisfaction with care (REPERES-33-G)	x	x	x	x
Relationship satisfaction (OMI-D)^a^	x	x	x	x
Sexuality (SBQ-G)	-	-	x	x

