#### Primary outcomes

Mental distress of patients (identified as mentally distressed by optimized screening, receive a psycho-oncology consultation and further diagnosis by psycho-oncology verifies mental distress) is the primary outcome. To assess distress, the German version of the National Comprehensive Cancer Network Distress Thermometer will be used (Mehnert et al. 2006a, b). General distress is measured on a visual analogue scale ranging from 0 = no distress to 10 = extreme distress. A score of 5 is internationally recommended as an indicator that a patient is distressed and needs support (National Comprehensive Cancer Network 2020). Further 36 potential causes of distress that are grouped in five subscales, i.e., (1) practical problems, (2) family problems, (3) emotional problems, (4) spiritual/religious concerns, (5) physical problems and an open answer option for possible other problems are assessed using the problem checklist (yes/no).

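### The covariates named for the primary ANCOVA do not include the t0 Distress Thermometer score, although it is collected in both sequential, non-randomised groups

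*Protocol article*

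**What the plan says.** Statistical measures states that the primary outcome, psychological distress, "is analyzed by ANCOVA (analysis of covariance) including variables such as tumor stage, age, and gender as covariates", and adds that this usually gives more power than a t test. Further on, the same section says that confounding is examined "using important covariates (age, gender, tumor entity, stage) as well as other theory-based influencing factors". It also says: "Before starting the analysis, the exact procedures are defined in a statistical analysis plan".

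On the data, Design states: "Measurement time points are a baseline measurement during the inpatient stay (t0) and a 3-month follow-up". Table 1 marks the DT at both time points in both groups. Primary outcomes describes the score: "General distress is measured on a visual analogue scale ranging from 0 = no distress to 10 = extreme distress". That section gives no time point for the primary comparison.

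On the design, the study is an uncontrolled before-and-after comparison. The comparison group (CG, 300 patients) is recruited on the same wards before the nurse training, and the intervention group (IG, 600 patients) after it.

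**The concern.** The article names covariates in two places, and in both it leaves out the patient's own earlier score on the outcome scale. That score is normally the first candidate for an ANCOVA of a repeated measure. The power gain that the article claims for ANCOVA depends on how well the covariates predict the outcome.

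Bias matters more than precision here. CG and IG come from different calendar periods, so their mean distress on entry can differ for reasons unrelated to the training. The protocol itself collects a Corona-DT for pandemic-related distress, so it recognises a source of distress that can change over time. Age, gender, stage and tumor entity need not capture such a shift. A t0 difference that is not modelled persists in part to t1 and is then read as a training effect. Recruiting more patients does not remove it.

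**Working it through.** **Is the primary comparison at t1?** No section says so outright. Sample size and power calculation asks for 190 evaluable patients per group for the primary analysis, then adds a dropout allowance to reach the number to be recruited at t0. Statistical measures imputes values missing through dropout. Loss after t0 matters to the primary analysis only if the outcome is measured later. The working below therefore takes t1 DT as the outcome.

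**Inputs from the protocol article:** effect size 0.3 (taken as a standardised mean difference, SD = 1); 190 evaluable per group; 80% power; 50% dropout; 300 CG and 600 IG patients planned.

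**Assumptions, not in the article:** two-sided alpha of 0.05; t0–t1 DT correlation ρ from 0.3 to 0.7; equal SDs at t0 and t1; a t0 difference of 0.2 SD between periods.

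**The plan's own figure.** n per group = 2 × (1.96 + 0.8416)² / 0.3² = 174.4, so 175 (176 with the t distribution). The stated 190 is not reproduced but errs on the safe side, with about 83% power. The step from 190 to 270 does not match 50% dropout either (190 / 0.5 = 380). That is a separate matter.

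**Precision.** With t0 DT in the model, the residual variance is 1 − ρ² times the unadjusted variance. At 50% retention of the planned sample, 150 CG and 300 IG patients are evaluable. The standard error without covariates is √(1/150 + 1/300) = 0.10, and power = Φ(0.3 / (0.10 × √(1 − ρ²)) − 1.96).

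**Carry-over.** With equal SDs, a t0 difference Δ that is not modelled adds ρ × Δ to the t1 difference.

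| ρ | Variance explained by t0 DT | n per group for 80% power | Power at 150 / 300 | Shift from Δ = 0.2 SD | Shift as share of 0.3 |
|---|---|---|---|---|---|
| no t0 DT | – | 175 | 85.1% | – | – |
| 0.3 | 9% | 159 | 88.2% | 0.06 SD | 20% |
| 0.5 | 25% | 131 | 93.4% | 0.10 SD | 33% |
| 0.7 | 49% | 89 | 98.7% | 0.14 SD | 47% |

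The row without t0 DT is a model with no covariates at all. The planned ANCOVA with stage, age and gender would do somewhat better, so the gains in the table are upper figures. Likewise, the shift would be smaller to the extent that the named covariates account for the t0 difference.

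**The case against.** The strongest objection is that the article does not say what the concern needs it to say. A reader might infer that the primary model leaves out baseline distress. The text does not support that: the first list is introduced by way of example, the second allows further theory-based factors, and the exact procedures go to an analysis plan that is not shown. This objection stands against any claim of exclusion. It does not dispose of the point, because the article names covariates and claims a power advantage for the model, and an analysis run with the named set would have the weakness described.

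A second objection is that no time point is stated. Primary outcomes also mixes the DT score with being identified by screening, receiving a consultation and having distress verified. If the comparison were at t0, or on that composite, there would be no earlier DT to adjust for, or the model would not apply as written. This stands as a condition; the dropout allowance and the imputation point to t1.

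Third, t0 in the IG comes after the nurse training, and the DT is itself the example of a screening tool used by the trained nurses. Adjustment could absorb part of an effect already present at t0. Taking the t0 score before any psycho-oncology consultation reduces this risk but does not remove it.

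Two other stronger readings fail. The absence of tumor entity from the first list might be read as a contradiction, but two open lists with different purposes do not contradict each other. The loss of precision might be read as leaving the trial underpowered, but at 150 and 300 evaluable patients power is about 85% without any covariate, above the 80% target. Finally, the article says that imputation uses all relevant information in the data set, so a lack of t0 DT there cannot be alleged.

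**Conclusion.** The point holds as a failure to name the main candidate covariate, and it is conditional on t1 DT being the primary comparison. On that condition, the named covariates give a less precise analysis than the collected data allow, and they leave the effect open to differences in entry distress between two non-randomised periods. The second consequence is the more serious: under the assumptions above, a 0.2 SD difference at t0 moves the estimate by 0.06 to 0.14 SD, which is 20% to 47% of the effect the trial is sized for. The article gives neither the correlation nor the size of any t0 difference, so these figures show scale and are not predictions. Adjusting for t0 DT would not remove other differences between the periods.

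**What to change.** - State DT at t1 as the primary outcome and time point.
- Name t0 DT, as a continuous variable, as a covariate in the primary ANCOVA alongside age, gender, stage and tumor entity.
- Define the t0 score as the one recorded before any psycho-oncology consultation, in the same way in both groups.
- Report the model without t0 DT as a sensitivity analysis, and interpret the two together in view of the timing of t0 in the IG.

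The cost is a few lines in the analysis section. The t0 and t1 scores are already scheduled in both groups, so no new measurement is needed. The one drawback is the possible absorption of an early effect, which the sensitivity analysis makes visible.

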## Materials and methods

### Participants

The study population includes inpatients of the visceral oncology centers at the three sites. The following inclusion criteria are defined: (a) diagnosis of a malignant solid tumor in the context of a visceral oncological disease (according to the survey form of Onkozert (2018): intestine, pancreas, stomach, liver, esophagus); (b) a minimum age of 18 years; (c) cognitive ability to consent to study participation. The following exclusion criteria are established: severe physical, cognitive, and/or language limitations (not be able to fill in questionnaires in German language).

All nurses at the visceral oncology centers at the three sites are expected to participate in the training during their working hours. Nurses were offered the opportunity to complete an evaluation before and after the training.

In addition, psycho-oncologists will also be asked about their experience with the overall screening process before and after the training, as well as patient distress.

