### Sample size and power calculation

Based on the primary cases in the centers, *n* = 200 patients per center will be included in the IG over a recruitment period of 24 months. For the CG, *n* = 100 patients per center will be recruited. Thus, a study population of *N* = 300 patients in the CG and *N* = 600 patients in the IG can be assumed.

For the primary analysis of the main outcome variable (mental distress of patients), small to medium effects of the IG compared to the CG are assumed. Assuming an effect size of 0.3, a sample size of *n* = 190 evaluable persons each in CG and IG are required for the primary analysis to be able to prove the assumed effect with a power of 80% (G*Power). With a dropout of 50%, a total of *n* = 270 patients per group (CG and IG) resulting in a total of *N* = 540 must be recruited at t0.

For the study, the case numbers of the participating oncology centers result in *N* = 1,533 cases per year. For the recruitment period of 24 months, a total pool of *N* = 3,066 can thus be expected. Thus, after subtracting the expected dropout rate of 50%, *N* = 1,533 patients can potentially be recruited for the study. Thus, the target sample size of *N* = 600 (IG) can be considered feasible. Since the CG will be recruited before the IG, the targeted sample size of* N* = 300 can also be considered feasible.

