*Notes* CG = comparison group; IG = intervention group; NCCN-DT = National Comprehensive Cancer Network Distress Thermometer (Mehnert et al. 2006a, b); Corona-DT = Adapted version of the DT to measure psychological distress from the Covid-19 pandemic, PHQ-9 = Depression module of the Patient Health Questionnaire (Kroenke et al. 2001); GAD-7 = Generalized Anxiety Disorder Questionnaire (Spitzer et al. 2006); SF-8 = Short Form-8 Health Survey (Ware et al. 2001); PA-F-KF = Fear of progression Questionnaire, short version (Mehnert et al. 2006a, b); HLS-EU-Q16 = European Health Literacy Questionnaire (Sorensen et al. 2013); SCNS-SF34-G = Supportive Care Needs Survey, short form (Sklenarova et al. 2015); ISSS/SSUK-8 = The Illness-specific Social Support Scale (Ullrich and Mehnert 2010); BIS = Body Image Scale (Hopwood et al. 2001); PAM-13D = Patient Activation Measure (Brenk-Franz et al. 2013); REPERES-33-G = Recherche Evaluative sur la Performance des Réseaux de Santé, German short version (Defossez et al. 2007); QMI-D = Quality of Marriage Index (Zimmermann et al. 2015); SBQ-G = Sexual Behavior Questionnaire (Müller and Gensch 2003)

^a^only for patients in relationships

All patients are given a code to ensure anonymity. All study documents will be stored in locked cabinets, and data will be stored in password-protected files accessible only to the study team.

The comparison sample (CG) is collected at baseline as a care-as-usual condition. The survey will take place before the OptiScreen-Training is conducted.

To survey the intervention group (IG), after conducting the oncology nursing training, the trained nurses are assigned per site to conduct the screening. Their task is to screen all inpatients for psychosocial distress using the screening instrument, e.g., the Distress Thermometer (Mehnert et al. 2006a, b). The nurses evaluate the screening and also consider the clinical impression of the treatment team. When performing the screening, the nurses take into account the aspects taught in the training regarding framework conditions and obstacles. In case of elevated distress, further psycho-oncological diagnosis and care is provided by the psycho-oncology team, which in turn provides feedback on the patient's psychological distress to the medical treatment team in a feedback loop. If there is no to low stress, a low-threshold information offer (e.g., flyer) is made.

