**Fig. 3 Fig3:**
[figure not shown]
Modules of the OptiScreen-Training

For the successful implementation of the screening process after training, a local study nurse supports the nursing staff at all three sites in the implementation and evaluation of the screening as well as the referral to psycho-oncology. With the help of the study nurse, the nurses try to overcome barriers and obstacles of the patients regarding the screening through advisory exchange with each other. The study nurse is in direct exchange with the psycho-oncology team. She is also a multiplier for the optimized screening in the medical team (e.g. nurses, casemanagement, physicians) and answers questions regarding the process or specific cases. The study nurse tries to reduce barriers and obstacles in communication and utilization of the screening and to optimize the implementation in the daily clinical routine.

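### Group is set by period within three sites, but the primary ANCOVA does not name site and the sample size treats patients as independent, so the nominal p-value and 80% power assume that all sites change alike

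*Protocol article*

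**What the plan says.** **Allocation.** The Design section states: "The study design is uncontrolled before and after pilot study". Comparison patients are recruited "on the same wards as after the introduction of the optimized screening". Under Participants, "All nurses at the visceral oncology centers at the three sites are expected to participate in the training during their working hours". Under Procedure and recruitment (Patients), "the trained nurses are assigned per site to conduct the screening", and in the section on the training "a local study nurse supports the nursing staff at all three sites in the implementation". Every site therefore contributes both groups, and all patients of a site change condition together.

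**Planned numbers.** Sample size and power calculation gives 200 IG patients per center and, for the other group: "For the CG, *n* = 100 patients per center will be recruited". It requires 190 evaluable per group for an effect size of 0.3 at 80% power. It mentions no intraclass correlation, design effect or site term.

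**Analysis.** Statistical measures assigns ANCOVA to the primary outcome, "including variables such as tumor stage, age, and gender as covariates". A later list for confounding has age, gender, tumor entity and stage, plus further theory-based factors. Neither list names site, ward or period. After the text turns to secondary outcomes it says that "binary or ordinal logistic mixed model regressions and linear mixed model regressions will be used", without naming a clustering unit. Exact procedures are left to a statistical analysis plan.

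**The concern.** A patient-level ANCOVA takes its standard error from the spread between patients within groups. The comparison, however, is between periods, and only three sites went through the change. Two things can go wrong.

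- **Site imbalance.** If one site supplies a larger share of evaluable CG than of evaluable IG patients, its usual level of distress enters the group difference. With 50% dropout expected, equal ratios among evaluable patients are planned but not assured.
- **Site-by-period variation.** If distress moves differently at the three sites between periods, for reasons other than the training, that variation does not shrink with more patients. The model does not see it.

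The protocol gives reasons to expect some of the second. Usual care is whatever each ward customarily does, the study nurse is local, training may be given on one day or three dates, and pandemic-related distress is measured because it was an influence of the period. At stake is whether a small p-value can support a multicenter best-practice claim.

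**Working it through.** **Inputs.** Effect size 0.3, power 80%, 190 evaluable per group, 50% dropout, and 100 CG and 200 IG per center at three centers (all from Sample size and power calculation). At 50% dropout this leaves 50 and 100 evaluable per site, so 150 vs 300. Alpha is not stated; 5% two-sided is assumed. The protocol gives no variance component, so those below are assumptions, expressed as shares of a total variance of 1.

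**Step 1: the plan's own figure.** A two-sided comparison of independent patients at d = 0.3 and 80% power needs 175 per group (normal approximation) or 176 (t test). The stated 190 is not reproduced; it gives power of about 0.83. Its surplus is no real clustering allowance. The variance allowed for 80% power is (0.3 / 2.8016)² = 0.01147, and 2/190 = 0.01053, leaving 0.00094. With three sites, 2τ²/3 = 0.00094 gives τ² = 0.0014, a share of 0.14%.

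**Step 2: site-by-period variation.** With τ² the variance of a site-period around its expected level,

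Var(difference) = 1/150 + 1/300 + 2τ²/3, against the patient-level value 1/150 + 1/300 = 0.0100 (SE 0.100).

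With r = true SE / 0.100, type I error is 2[1 − Φ(1.96/r)] and power is Φ(0.3/SE − 1.96).

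| Assumed share τ² | Variance | True SE | r | Type I error | Power, correct SE |
|---|---|---|---|---|---|
| 0 | 0.0100 | 0.100 | 1.00 | 5.0% | 85% |
| 0.005 | 0.0133 | 0.115 | 1.155 | 9.0% | 74% |
| 0.01 | 0.0167 | 0.129 | 1.291 | 12.9% | 64% |

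A variant that holds total variance at 1 gives 8.9% and 12.8%. The term 2τ²/3 does not depend on the number of patients. Once it reaches 0.01147 (τ² = 0.01147 × 3/2 = 0.017), no recruitment gives 80% power with three sites.

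**Step 3: does a fixed site effect help?** Simulated type I error of the patient-level model with 50 and 100 evaluable at each site:

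| Site share | Site-by-period share | Without site | With fixed site |
|---|---|---|---|
| 5% | 0 | 4.3% | 4.6% |
| 2% | 0 | 4.8% | 4.9% |
| 2% | 1% | 13.1% | 13.5% |
| 2% | 2% | 20.2% | 20.8% |

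With the planned ratio, leaving site out costs nothing. With site-by-period variation, adding it repairs nothing.

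**Step 4: when the ratio drifts.** As an illustration, take evaluable CG of 30 / 50 / 70 and IG of 120 / 100 / 80, so the totals stay 150 and 300. The sites' shares are 0.20 / 0.33 / 0.47 of CG and 0.40 / 0.33 / 0.27 of IG. The squared differences sum to 0.20² + 0² + 0.20² = 0.08. Without site in the model, the true variance is (1 − σ²)(0.01) + 0.08σ² for a site share σ².

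- σ² = 2%: 0.0098 + 0.0016 = 0.0114, r = 1.068, type I error 6.6%.
- σ² = 5%: 0.0095 + 0.0040 = 0.0135, r = 1.162, type I error 9.2%.

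A simulation of this example gave 7.0% and 8.9% without site, and 5.3% and 5.0% with it. Here the site term does its job.

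**The case against.** **This is a condensed article, and a site term is ordinary content for an analysis plan.** This largely stands as a limit on the wording. The covariate lists are open, an analysis plan is announced, and nothing excludes site. A reader might infer that the plan has decided to leave site out; the text supports only that site is not named. What remains is more than silence: the primary model is fixed as ANCOVA, covariates are listed twice without site, and the sample size is already set on independent patients.

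**Site is crossed with group, not nested in it.** Correct. A reader might infer from delivery to whole sites that leaving out site by itself invalidates the standard error. Step 3 shows that it does not while the planned ratio holds; the error rate is then nominal or slightly below.

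**The size rests on an assumed variance.** Also correct. At zero site-by-period variance the test has its nominal level. The range shows sensitivity, not a forecast.

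**A one-site result need not stay hidden.** Sensitivity analyses for consistency are planned, and imputation is meant to use all relevant information, which could include site. Neither is said to be done by site, so the request to show site results stands, but not a claim that they would be concealed.

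**The study calls itself a pilot.** It does, and that supports an exploratory p-value. The protocol nevertheless presents a power calculation to prove an effect.

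**Conclusion.** The point holds in a limited form. The primary analysis and its sample size treat patients as independent, although the condition is set for six site-periods. Confounding by site arises only if evaluable CG:IG ratios differ between sites; in the illustration it raises type I error to about 7–9% for site shares of 2–5%, and a fixed site effect restores about 5%. Understatement of the standard error arises only if sites change differently between periods. For shares of 0 / 0.5% / 1%, type I error is about 5% / 9% / 13%, and power at d = 0.3 with the correct standard error about 85% / 74% / 64%. These figures assume 150 vs 300 evaluable, a two-sided 5% test and the normal approximation.

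Two stronger conclusions are not supported. Adding site to the model does not make the p-value sound, since six site-periods do not allow a reliable cluster-level standard error. Nor should a claim of benefit require the same direction at all three sites. With 50 vs 100 per site the SE is √(1/50 + 1/100) = 0.173. Under a uniform true d = 0.3 each site is positive with probability Φ(0.3/0.173) = 0.958, all three with 0.958³ = 0.88, so the rule would block a true effect about 12% of the time.

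**What to change.** In the analysis plan:

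1. Name site (three levels) as a fixed effect in the primary ANCOVA and in the imputation model. State that this deals with unequal group ratios across sites and does not correct for site-by-period variation.
2. Report the CG–IG difference for each site with its confidence interval, and the site-by-group interaction.
3. Add a sensitivity analysis that recomputes the standard error and p-value over a range of assumed site-by-period variance shares, starting at zero.
4. State that the 80% power and the nominal p-value assume no site-by-period variation, that three sites cannot support a reliable cluster-level standard error, and that the p-value is therefore exploratory, in keeping with the pilot label.

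Cost: two degrees of freedom, one extra table and a more cautious claim. No change to recruitment or data collection is needed.
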